
**Table 1 Tab1:** Diagnostic criteria for MetS as agreed in the Consensus Statement published in Alberti et al., 2009

Diagnostic criteria	Threshold values
Waist circumference	≥ 102 cm (M); ≥ 88 cm (F)
Fasting plasma glucose	≥ 100 mg/dL or specific treatment
Blood pressure	≥ 130/85 mmHg or specific treatment
Triglycerides	≥ 150 mg/dL or specific treatment
HDL cholesterol	< 40 mg/dL (M); < 50 mg/dL (F) or specific treatment

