Fagestrom scale (Heatherton et al. 1991)	Self-report tool used to assess nicotine dependence in individuals who smoke cigarettes	6	0–10	IT, FR, DE, NO, ESP
Mini-Mental State Examination (MMSE) (Folstein et al. 1975)	Screening tool used to assess cognitive impairment	11	0–30	IT, FR, DE, NO, ESP
Handgrip squeeze test (Sayer et al. 2006)	It measures the maximum isometric strength of the hand and forearm muscles			
Knee extension test (Bohannon 1986)	It measures the hamstring muscle length and the range of active knee extension in the position of hip flexion			

Assessments will be conducted through participants' illness history and BD treatments. A structured physical examination, based on the Physical Examination Essential Checklist (Additional file 1), will be administered, with any signs of ill health promptly reported to clinicians.

During the physical examination, patients will complete the Knee extension test (Bohannon 1986) and the handgrip squeeze test (Sayer et al. 2006) measured through a dynamometer. Additionally, clinical electrocardiograms (ECGs) will be performed to identify QTc prolongation or the presence of arrhythmias. The primary aim of the ECS is to identify common associations among the five MetS diagnostic criteria in patients with BD at both T0 and T1 using clustering techniques and multiple correspondence analyses. Each stratum within each site will include approximately 14 subjects, totaling approximately 57 patients from the 400-sample pool, ensuring data representativeness and statistical power. The 1-year follow-up phase will begin immediately after the baseline assessment. At the end of this period, participants will undergo reassessment using a set of tools (Additional file 1: Table S3) to evaluate the clinical progression or improvement in MetS criteria, focusing on changes among patients meeting these criteria.

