##### Biological measures

MetS is defined based on clinical and laboratory measurements (Alberti et al. 2009) and is strongly associated with metabolic liver disease, considered by some authors as an additional component of the syndrome (Kotronen et al. 2009; Kotronen and Yki-Järvinen 2008). There is a myriad of biomarkers associated with MetS that are either included in the pathway to its development and can help in its prediction or are potential mediators of its outcomes. They have been categorized into cardiometabolic, dyslipidemias, markers of oxidative stress, and inflammatory markers (Robberecht and Hermans 2016). Cardiometabolic biomarkers include insulin resistance, thyroid function, and cortisol levels, with the latter two being particularly relevant for patients with BD (Chakrabarti 2011; Dziurkowska and Wesolowski 2021). Adipokines, including adiponectin and leptin, are significantly associated with MetS, with its ratio being proposed as a biomarker of adipose tissue dysfunction (Lee and Shin 2020). Dyslipidemias involve elements additional to those required for MetS definition (Robberecht and Hermans 2016). Furthermore, oxidative stress markers like oxidized low-density lipoprotein (OxLDL) are linked to MetS and its consequences (Holvoet et al. 2008). Inflammation plays a crucial role in MetS, with markers such as high-sensitivity C-reactive protein (hsCRP), serum amyloid A, and cystatin C being associated (Robberecht and Hermans 2016; Magnusson et al. 2013; Ridker 2007). A systematic literature review (Srikanthan et al. 2016) has informed the selection of various biomarkers for MetS, including additional analytes to those mentioned so far: pro-inflammatory cytokines (interleukin-6—IL-6, Tumour Necrosis Factor-alpha—TNF-α), markers of pro-oxidant status (OxLDL, uric acid), and leptin, which are increased in MetS. There is limited available information on most of these biomarkers in this population, as well as their relationship with psychometric variables both cross-sectionally and longitudinally. During the ECS, patients will also be asked to undergo two blood and two saliva samples, one at T0 and one at 1-year follow-up (T1): 24 selected measurements and biomarkers, shown in Table 5, will be collected, shipped to a centralized laboratory, and assessed.

**Table 5 Tab5:** List of biomarkers to be assessed in the ECS and their normal ranges of values

Adiponectin/leptin ratio	According to the lab reference values
Core biomarkers	

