#### Study 3: the exploratory clinical study

Following the sign of informed consent, we will assess at baseline, the distribution of all possible combinations of the 5 MetS criteria (32 dispositions with repetition of two elements) among BD patients. A subject scoring positive at 3 criteria out of 5 will be defined as MetS + . At baseline, MetS + subjects will be compared to MetS—(less than 3 out of 5 criteria) for 15 predefined items, using either t-test for independent samples (continuous items) or Fisher Exact test (for binary items). Due to test multiplicity, individual tests p-value will be adjusted using Benjamini–Hochberg procedure.

The evolution in MetS status (MetS + /MetS−) from baseline to 1 year follow-up will be evaluated using multistate models, in order to identify what items might affect the transition probabilities. The 5 MetS criteria combinations will be explored using multiple correspondence analyses in order to identify possible clusters based on the predefined items. All the analyses will be performed using R (R Foundation, version 4.3.1 or newer). All tests will be two-sided.

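### Four of the five MetS criteria are met by treatment alone, so T0-to-T1 transitions in MetS status mix treatment starts and stops with measured metabolic change

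*Protocol article*

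**What the plan says.** Table 1 (Background) lists five criteria. The blood pressure row reads "≥ 130/85 mmHg or specific treatment", and the rows for fasting glucose, triglycerides and HDL cholesterol carry the same treatment alternative. The waist row gives sex-specific thresholds only.

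Data analyses, Study 3, turns the criteria into a status: "A subject scoring positive at 3 criteria out of 5 will be defined as MetS" positive, and fewer than three is MetS negative. The same section then states: "The evolution in MetS status (MetS + /MetS−) from baseline to 1 year follow-up will be evaluated using multistate models". The purpose is to find which items affect the transition probabilities.

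Clinical measures (Study 3) gives the aim of the 1-year visit: "to evaluate the clinical progression or improvement in MetS criteria, focusing on changes among patients meeting these criteria". The Aims section also names the 1-year incidence of MetS as an objective of this study, and Digital measures plans to predict change in the MetS components from activity and circadian variables.

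Treatment-related data are recorded in the Patient Schedule at T0 and over the follow-up year (Clinical measures). The article does not say how a start or stop of specific treatment between the two visits is handled when change is scored. The only drug items among the 15 variables in Table 6 are psychotropic (lithium or mood stabilizers, and antipsychotics, each as ever treated).

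**The concern.** A definition that counts treated disease as present suits prevalence at one visit. Used at two visits to measure change, it makes a criterion depend on two things that can move in opposite directions: the measured value and the treatment. A patient whose blood pressure falls below threshold on a drug started after T0 is recorded as unchanged. A patient who comes off a drug and stays within threshold is recorded as improved. A patient given a drug during the year is recorded as newly meeting the criterion, whatever the measured value.

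At stake is the meaning of the transition results. An item associated with a MetS transition may be associated with metabolic change, with treatment being started or stopped, or with both, and the planned output gives no way to tell these apart.

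**Working it through.** **Plan's own figure.** The article counts "32 dispositions with repetition of two elements" for the five criteria. Five yes/no criteria give 2^5 = 32, so the figure is reproduced, and it confirms that each criterion is scored as binary with treatment folded in.

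**Rule per criterion.** For the four criteria with a treatment alternative, met = (value beyond threshold) OR (on specific treatment). For waist, met = (value beyond threshold). Applied at both visits:

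| Criterion | T0 | T1 | Scored |
|---|---|---|---|
| Treatable | beyond threshold, untreated | in range, treated | met to met: no improvement |
| Treatable | treated | in range, untreated | met to not met: improvement |
| Treatable | treated | beyond threshold, untreated | met to met: no change |
| Treatable | in range, untreated | in range, treated | not met to met: progression |
| Waist | beyond threshold | in range | met to not met, whatever the treatment |

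Stopping treatment therefore counts as improvement only if the value is within threshold off treatment.

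**From criterion to status.** MetS-positive patterns are those with at least three criteria met: C(5,3) + C(5,4) + C(5,5) = 10 + 5 + 1 = 16 of 32. Take the extreme case in which every met treatable criterion is put on treatment and every measured value, waist included, is normal at T1.

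- Patterns with three or four treatable criteria met: (C(4,3) + C(4,4)) × 2 waist states = (4 + 1) × 2 = 10. All 10 are still scored MetS positive although no measured value is abnormal.
- Patterns with waist plus exactly two treatable criteria: C(4,2) = 6. These become MetS negative, through waist alone.
- If waist stays beyond threshold, these 6 also remain positive, so all 16 do.

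These are counts of patterns, not shares of patients.

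**Scale.** The article gives no rate of treatment start, treatment stop or normalisation, so the size can only be illustrated. Its stated proportion of 31% gives 400 × 0.31 = 124 MetS-positive patients, while its group split in Power and sample size gives 180; both are carried. With the 20% dropout allowance, 124 × 0.8 = 99 to 180 × 0.8 = 144 are followed. Assume a share normalises on newly started treatment in a way that decides status, meaning MetS negative on values but positive under Table 1:

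| Assumed share | of 99 | of 144 |
|---|---|---|
| 5% | 5 | 7 |
| 10% | 10 | 14 |
| 20% | 20 | 29 |

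**The case against.** **Treated disease is still disease.** Counting a controlled, treated criterion as present is the consensus definition the article adopts, and transitions in MetS so defined are a coherent target that fits the 1-year incidence objective. Someone off treatment and in range no longer meets the criterion. Someone who starts treatment may have crossed the threshold between visits. This stands, and it is why the Table 1 definition should remain the main one. It does not make the transitions readable as measured metabolic improvement or deterioration.

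**The analysis plan may cover it.** That plan is not shown. But the article itself fixes the definition, the two states and the model, and the mixing follows from these three together. What remains fair is that Clinical measures does not say whether improvement in the criteria is judged on status or on values; only the status transition is explicitly binary.

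**Stronger readings.** Three might be inferred, and the article supports none of them.

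- That a patient who is treated and normalises cannot show improvement at all. This is true of the treated criterion only; status can still change through waist or through a criterion that normalises untreated.
- That the study itself provokes the treatment. Findings at the structured physical examination are handled "with any signs of ill health promptly reported to clinicians", but of the four treatable criteria only blood pressure would ordinarily be found there, and the checklist is in a file not shown. Blood samples "will be collected, shipped to a centralized laboratory, and assessed", with no stated return of results to clinicians. That reporting leads to treatment is an inference, and the point does not need it: any start or stop during the year has the same effect.
- That the transition results distort the Clinical Support Tool, or that particular items will falsely predict persistence. The Discussion names baseline data of this study for the tool's retrospective validation; it does not say the transition model enters it. Confounding of items linked to being treated is possible, but not shown.

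**Conclusion.** The point holds at the level of the criterion. Four of the five criteria can be met by treatment alone, so the planned T0-to-T1 transitions in binary MetS status combine treatment starts and stops with measured change, and nothing in the article separates them. It does not hold as a statement about every treated patient.

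The logical result needs only Table 1, the three-of-five rule and the binary transition model. The number of patients affected cannot be derived from the document. The illustration of 5 to 29 patients rests wholly on an assumed 5% to 20% share and on which of the article's two MetS-positive counts applies; it should not be read as an estimate.

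This is a limit on what the transition results can support and a cheap improvement, not an error in the MetS definition or in the baseline comparison.

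**What to change.** Keep the Table 1 definition for baseline prevalence and as the main definition of MetS status. For the T0-to-T1 analysis add two things:

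1. Repeat the transition analysis with all criteria scored on measured values alone at both visits.
2. For each of glucose, blood pressure, triglycerides and HDL, report how many patients started and how many stopped specific treatment between T0 and T1, beside the corresponding transitions.

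State also whether improvement in the criteria at T1 refers to status, to measured values, or to both.

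No new data should be needed: values and treatment are both required to score Table 1, and treatment-related data are recorded at T0 and T1. The cost is some extra analysis and a table. The repeat has its own limit: an in-range value under treatment reflects controlled rather than absent disease, so it supplements the main analysis and does not replace it.

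Replacing the binary criteria with three states (in range untreated, in range treated, beyond threshold) is not recommended as the main route. Four three-state criteria plus binary waist give 3^4 × 2 = 162 patterns instead of 32, for 400 × 0.8 = 320 patients followed, and it is not clear how they would map to the three-of-five rule.

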##### Biological measures

MetS is defined based on clinical and laboratory measurements (Alberti et al. 2009) and is strongly associated with metabolic liver disease, considered by some authors as an additional component of the syndrome (Kotronen et al. 2009; Kotronen and Yki-Järvinen 2008). There is a myriad of biomarkers associated with MetS that are either included in the pathway to its development and can help in its prediction or are potential mediators of its outcomes. They have been categorized into cardiometabolic, dyslipidemias, markers of oxidative stress, and inflammatory markers (Robberecht and Hermans 2016). Cardiometabolic biomarkers include insulin resistance, thyroid function, and cortisol levels, with the latter two being particularly relevant for patients with BD (Chakrabarti 2011; Dziurkowska and Wesolowski 2021). Adipokines, including adiponectin and leptin, are significantly associated with MetS, with its ratio being proposed as a biomarker of adipose tissue dysfunction (Lee and Shin 2020). Dyslipidemias involve elements additional to those required for MetS definition (Robberecht and Hermans 2016). Furthermore, oxidative stress markers like oxidized low-density lipoprotein (OxLDL) are linked to MetS and its consequences (Holvoet et al. 2008). Inflammation plays a crucial role in MetS, with markers such as high-sensitivity C-reactive protein (hsCRP), serum amyloid A, and cystatin C being associated (Robberecht and Hermans 2016; Magnusson et al. 2013; Ridker 2007). A systematic literature review (Srikanthan et al. 2016) has informed the selection of various biomarkers for MetS, including additional analytes to those mentioned so far: pro-inflammatory cytokines (interleukin-6—IL-6, Tumour Necrosis Factor-alpha—TNF-α), markers of pro-oxidant status (OxLDL, uric acid), and leptin, which are increased in MetS. There is limited available information on most of these biomarkers in this population, as well as their relationship with psychometric variables both cross-sectionally and longitudinally. During the ECS, patients will also be asked to undergo two blood and two saliva samples, one at T0 and one at 1-year follow-up (T1): 24 selected measurements and biomarkers, shown in Table 5, will be collected, shipped to a centralized laboratory, and assessed.

**Table 5 Tab5:** List of biomarkers to be assessed in the ECS and their normal ranges of values

Adiponectin/leptin ratio	According to the lab reference values
Core biomarkers	
Alanine transaminase (ALT)	< 55 U/L
Aspartate transaminase (AST)	< 34 U/L
C Peptide	0.81–3.85 ng/mL
Fasting plasma glucose	70–99 mg/dL
Gamma-Glutamyl Transferase (GGT)	< 73 U/L (males); < 38 U/L (females)
High-density lipoprotein (HDL)-cholesterol	≥ 40 mg/dl (males); ≥ 50 mg/dl (females)
hsCRP	≤ 0,3 mg/L
Oxidized LDL	20–170 ng/mL
Triglycerides	< 150 mg/dL low risk; 150–199 mg/dL moderate risk; 200–499 mg/dL high risk; > 500 mg/dL very high risk
Additional biomarkers	
Albumin	3.4–5.0 g/dL
Cystatine-C	0.56–0.95 mg/L
IL-6	< 4,4 pg/mL
LDL-cholesterol	< 55 mg/dL very low risk individuals; 55–70 mg/dL low risk individuals; 70–100 mg/dL moderate risk individuals; 100–116 mg/dL very high-risk individuals; > 116 mg/dL extreme risk
Salivary cortisol	Morning: 0.32–10.76 ng/mL Evening: 0.06–2.74 ng/mL
Serum amyloid A	< 6,4 mg/L
Testosterone	Males: 1.97–6.69 ng/mL (< 50 years); 1.87–6.84 ng/mL (≥ 50 years). Females: 0.08–0.35 (< 50 years); 1.87–6.84 (≥ 50 years)
Thyroid antibodies (TPOAb)	< 60.0 U.I./mL
Thyroid antibodies (TGAAb)	< 0.9–4.1 U.I/mL
TNF-α	4.6–12.4 pg/mL
Total cholesterol	< 200 mg/dL
Thyroid-stimulating hormone (TSH)	0.55–4.78 micUl/ml (> 18 years)
Uric acid	3.5–7.2 mg/dL (males); 2.6–6.0 mg/dL (pre-menopause females); 3.5–7.2 mg/dL (post-menopause females)

##### Digital measures

During the ECS, we will employ a digital tool to measure PA and sleep patterns. We will compare about 100 patients who meet (MetS +) or do not meet (MetS−) MetS diagnostic criteria at baseline (about 20 per country) with 100 psychologically healthy control subjects (about 20 per country), matched for both age (by 10-year age group) and sex. Healthy controls will be interviewed to obtain sociodemographic data and information on health status, specifically regarding psychological, cardiovascular, or metabolic diseases. Patients with BD and healthy controls will wear ActiGraph GT9X Link or ActiGraph GT3X devices three times during a year, each time lasting 1 week totalling 3 weeks over a year to assess total PA, intensity-specific PA, sedentary time, and circadian rhythms. In both groups, we will explore associations between PA and different variables, (such as sedentary time, sociodemographic characteristics, and clinical markers) using generalized linear mixed models (GLMM). These models will consider wear time, various activity levels, heart rate, inter-daily stability, intra-daily variability, and rhythm amplitude as factors. Additionally, PA and circadian rhythm variables will predict changes in MetS components between baseline and follow-up assessments. In the same week during the measurement via ActiGraph, the same subgroup of patients undergoing PA monitoring will also complete a dietary assessment using the MyFood24 web portal. Furthermore, the ECS includes an ESM study, prompting patients eight times daily via smartphone to report mood, stressors, eating behaviour, and other variables. This signal-contingent reporting will be complemented by event-contingent reports of eating episodes. This approach will ensure comprehensive data collection in natural settings, will avoid lengthy retrospective self-reports, and will capture participants' environmental, social, and psychological states.

### Data analyses

#### Data quality management

Data quality management and storage are critical aspects of any biomedical study. These processes ensure that the data collected during the study are accurate, reliable, and securely stored for analysis and future reference. In order to guarantee appropriate data quality management, we will adopt the following steps:(i)Data collection protocols: we will develop well-defined data collection protocols to ensure consistency in data gathering. These protocols may include standardized procedures, guidelines, and training for data collectors to minimize errors and biases.(ii)Data validation: we will use validation procedures to check the integrity and accuracy of the data. This involves cross-verifying data entries, identifying outliers, and resolving any inconsistencies or missing values.(iii)Data cleaning: data cleaning involves the process of correcting errors, removing duplicates, and addressing missing or erroneous data points. This step is essential for ensuring the reliability of the final dataset.(iv)Quality control: regular quality control checks will be performed throughout the study to identify and rectify any potential issues with data collection or recording. These checks will help maintain data accuracy and completeness.(v)Data monitoring: continuous monitoring of the data collection process will allow study researchers to identify any deviations from the established protocols and take corrective actions promptly.(vi)Data auditing: an independent review or audit of the data can be performed to validate the accuracy and compliance of the data with study protocols and ethical guidelines.

#### Study 1: the registry study

For prediction modelling studies in Sweden, we will employ multivariate Cox proportional hazards regression analysis to develop 1-, 2- and 5-year risk prediction models separately for: CVD, and type 2 diabetes, as primary outcomes, as well as for proxy measures of MetS—hypertension, obesity and hyper/dyslipidaemia, and all-cause and cause-specific mortality as secondary outcomes, in individuals with BD. This will be done by combining traditional risk factors of cardiometabolic disorders (i.e., age, sex, a diagnosis/medication prescription for hypertension, diabetes mellitus (type 1 and type 2), hyperlipidaemia, obesity, and smoking; and family history), with potentially relevant novel predictors associated with both BD and an increased risk of cardiometabolic conditions (i.e., psychiatric comorbidity, use of psychotropic medication, and socio-demographic factors). We will use a limited backward stepwise procedure to determine whether to retain novel candidate predictors based on their p-values. Traditional risk factors will be kept in the model. With this approach we aim to retain predictors considered as traditional cardiometabolic risk factors based on clinical practice and previous studies, and to consider potentially relevant novel risk factors, with the final model being easily applicable by clinician, with satisfactory face validity. A bootstrapping method will be used for internal validation of the models with 200 bootstrap samples. To assess the discrimination of the models, the ROC curve and C-index will be used. To assess the calibration of the models we will use the Integrated Brier Score and calibration plots. We will also compare the performance of the models that includes only traditional risk factors with the models that include additional novel risk factors by calculating the Net Reclassification Index (NRI) and the Integrated Discrimination Improvement (IDI) index. We will also test the performance of the models across the following subgroups: males/females, and aged younger than 50/50 and older. Machine Learning (ML) algorithms for survival analysis will be tested on Swedish and Norwegian register data, considering a large number of available potential risk indicators such as demographics, electronic medical records, and genotypes. The overarching research question is to explore if ML algorithms based on many predictors may improve the predictive accuracy. For the ML algorithms, the data will be split into a 60% training set, 20% validation set, and 20% test set. Four models will be trained: penalized Cox regression, random survival forest, gradient boosting machine, and survival support vector machine. Hyperparameters will be tuned on the validation set. Model discrimination will be evaluated with C-index and cumulative/dynamic AUC. Calibration will be assessed with the Integrated Brier Score. Performance metrics on the test set will determine the final model. Sensitivity analyses will explore model accuracy when considering predictors related to patient history and dispensed medications only. We will also assess model performance separately in Sweden and Norway. Furthermore, we will merge register data from Norway and Sweden with biobank data (N ~ 1.3 million) to evaluate whether adding genotypes improves predictive power.
